## Abstract

**Background:**

Daily and event-driven HIV pre-exposure prophylaxis (PrEP) with oral tenofovir-emtricitabine is highly effective to prevent HIV in men who have sex with men (MSM). PrEP care generally consists of in-clinic monitoring every 3 months that includes PrEP dispensing, counseling, and screening for HIV and sexually transmitted infections (STIs). However, the optimal frequency for monitoring remains undetermined. Attending a clinic every 3 months for monitoring may be a barrier for PrEP. Online-mediated PrEP care and reduced frequency of monitoring may lower this barrier.

**Objective:**

The primary objective of this study is to establish the noninferiority of online PrEP care (vs in-clinic care) and monitoring every 6 months (vs every 3 months). The secondary objectives are to (1) examine differences between PrEP care modalities regarding incidences of STIs, HIV infection, and hepatitis C virus infection; retention in PrEP care; intracellular tenofovir-diphosphate concentration; and satisfaction, usability, and acceptability of PrEP care modalities; and (2) evaluate associations of these study outcomes with sociodemographic, behavioral, and psychological characteristics.

**Methods:**

This study is a 2×2 factorial, 4-arm, open-label, multi-center, randomized, controlled, noninferiority trial. The 4 arms are (1) in-clinic monitoring every 3 months, (2) in-clinic monitoring every 6 months, (3) online monitoring every 3 months, and (4) online monitoring every 6 months. The primary outcome is a condomless anal sex act with a casual partner not covered or insufficiently covered by PrEP (ie, “unprotected act”) as a proxy for HIV infection risk. Eligible individuals are MSM, and transgender and gender diverse people aged ≥18 years who are eligible for PrEP care at 1 of 4 participating sexual health centers in the Netherlands. The required sample size is 442 participants, and the planned observation time is 24 months. All study participants will receive access to a smartphone app, which contains a diary. Participants are requested to complete the diary on a daily basis during the first 18 months of participation. Participants will complete questionnaires at baseline and 6, 12, 18, and 24 months. Dried blood spots will be collected at 6 and 12 months for assessment of intracellular tenofovir-diphosphate concentration. Incidence rates of unprotected acts will be compared between the online and in-clinic arms, and between the 6-month and 3-month arms. Noninferiority will be concluded if the upper limit of the 2-sided 97.5% CI of the incidence rate ratio is <1.8.

**Results:**

The results of the main analysis are expected in 2024.

**Conclusions:**

This trial will demonstrate whether online PrEP care and monitoring every 6 months is noninferior to standard PrEP care in terms of PrEP adherence. If noninferiority is established, these modalities may lower barriers for initiating and continuing PrEP use and potentially reduce the systemic burden for PrEP providers.

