## Methods

### Study Objectives

The primary objective of the EZI-PrEP study is to assess whether online-mediated PrEP care is noninferior to standard in-clinic care and whether monitoring every 6 months is noninferior to standard monitoring every 3 months. We defined the primary outcome measure as a condomless anal sex act with a casual partner during which PrEP was not used or insufficiently used (herein referred to as an “unprotected act”). Ideally, incident HIV infection would be the primary outcome, but this outcome is expected to be exceedingly rare for use in a clinical trial [42]. The outcome “unprotected act” can be regarded as a behavior that carries the most risk for HIV acquisition and is expected to occur frequently enough to serve as the primary outcome.

The secondary objective is to compare differences between PrEP care modalities in the incidences of bacterial STIs (ie, chlamydia, gonorrhea, and syphilis), HIV infection, and HCV infection; intracellular concentrations of TFV-DP; retention in PrEP care; total number of STI consultations (in addition to PrEP monitoring visits); and satisfaction, usability, perceived quality, acceptability, and time and cost investments of PrEP care.

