### Data Analysis

#### Primary Outcome

The primary outcome (“unprotected act”) will be assessed using daily self-reported data on sexual behavior, pill intake, and condom use. We will use all available data, meaning that observation time and all data of those who are lost to follow-up or have dropped out will be included until their last day in the study. We will determine, for each day of follow-up, whether a condomless anal sex act with a casual partner took place. We will also determine whether sufficient PrEP pills were taken around the time of this condomless anal sex act. Using this information, the condomless anal sex act will be considered as either unprotected or not. We will then calculate the total number of unprotected acts (n) and the total person-years of observation. Incidence rates per 100 person years will be calculated by dividing the sum of all unprotected acts by the sum of person-years of observation and multiplying the result by 100. We will calculate the incidence rates among participants of online PrEP care (arms 3 and 4), in-clinic PrEP care (arms 1 and 2), monitoring every 6 months (arms 2 and 4), and monitoring every 3 months (arms 1 and 3). Two main analyses will be conducted in which we will test the ratio of the incidence rates of unprotected acts for (1) online PrEP care versus in-clinic PrEP care and (2) monitoring every 6 months versus monitoring every 3 months. The analyses will be based on crude unadjusted incidence rate ratios.

A noninferiority trial intends to demonstrate that one intervention is not unacceptably worse than a comparison intervention [54]. To do so, the lower limit of the 95% CI (or 2-sided 97.5% CI) should not extend beyond a predefined margin, which is referred to as the noninferiority margin. In this study, noninferiority will be tested using a 1-sided test based on maximum likelihood estimators with a type 1 error at 0.0125 (ie, with 2 comparisons using Bonferroni corrections=0.025/2) [40] and a noninferiority ratio of 1.8. If the upper 2-sided 97.5% CI of the incidence rate ratio is below 1.8, we will conclude that the intervention arms are noninferior to the comparator arms.

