## Discussion

We have designed the EZI-PrEP study in order to assess whether online-mediated PrEP care and a reduced frequency of monitoring are noninferior compared to standard practice. In this study, we will develop, implement, and rigorously evaluate an online-mediated PrEP care service and a less frequent monitoring schedule (every 6 months) among MSM and TGDP in 4 regions in the Netherlands. Studies in countries with concentrated HIV epidemics and PrEP programs for MSM show the potential of PrEP programs to reduce population-level HIV incidence [57,58]. Reducing the number of in-clinic visits may reduce the burden of PrEP care and might help increase uptake and improve retention. Additionally, it may improve access to PrEP as it may make more resources available and enlarge capacity at facilities providing PrEP. Online-mediated PrEP care and monitoring every 6 months are promising options to reduce in-clinic PrEP visits, but it is unclear how this affects PrEP adherence. Since both modalities involve less intense contact between PrEP users and health care providers, and thus less guidance in PrEP use, it could theoretically have an adverse effect on PrEP adherence. The EZI-PrEP study will be able to provide evidence on the efficacy and safety of online-mediated PrEP care and PrEP care every 6 months compared to standard in-clinic PrEP care every 3 months in terms of PrEP adherence as a proxy for HIV risk. If these services are found to be noninferior, both online access to PrEP and reduced monitoring frequency could become viable evidence-based PrEP care options.

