The EZI-PrEP study will contribute crucial data to the ongoing debate on optimal HIV and STI screening frequency for MSM who use PrEP. By comparing incidence rates of HIV infection, STIs, and HCV infection between the 3-month and 6-month monitoring study arms, we will provide evidence on the impact of testing every 6 months on STI diagnosis and treatment. If noninferiority in terms of PrEP adherence is concluded and STI incidence rates are similar between the 6-month and 3-month monitoring arms, a stronger case can be made to offer PrEP monitoring every 6 months as the standard of care. If STI incidence rates are not similar between the study arms, we will be able to examine to what extent this is related to particular sociodemographic, sexual behavior, or psychosocial factors and advise on implementation accordingly. EZI-PrEP study participants will be allowed to test for HIV, STIs, and HCV in between regular PrEP monitoring visits at their own initiative. The EZI-PrEP study will also be able to quantify the extent to which in-between visits occur among PrEP users receiving monitoring every 6 months.

Since adherence to the PrEP intake regimen is crucial for its effectiveness [3,5-7], having a thorough understanding of enabling and disenabling factors of PrEP adherence is important. The EZI-PrEP study will provide new insights on the associations between sociodemographic and psychosocial variables on the one hand and PrEP adherence on the other hand. Insights into the role of such sociodemographic and psychological factors in the context of adherence may be used to further improve the content or conduct of PrEP consultations and inform interventions that support PrEP adherence. Furthermore, we will investigate the relationship of these factors with PrEP adherence, STIs, retention, and satisfaction with PrEP care, according to the study arm. The results of these analyses could be used to determine if these new PrEP care modalities should be implemented widely or should be offered to specific subpopulations.

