The main methodological challenge of this study is the measurement of the primary outcome measure, which is based on self-reported PrEP intake and sexual behavior. In the AMPrEP study, it was found that reporting of daily data decreases over time, which may confront us with a substantial amount of missing data. We will therefore implement an intensive scheme of reminders. Additionally, the diary in itself may cause behavioral changes (ie, Hawthorne effect). For instance, PrEP intake may be affected due to the daily reminder to complete the diary. Completing the diary on a daily basis might also be too burdensome for some participants, and as a result, their motivation to complete the study could be low. However, because of randomization, any effect of daily diary entry on behavior or participation is not expected to differ across the 4 arms. A major strength of our study is that it is embedded in routine PrEP care, which increases the generalizability of study outcomes and will provide a realistic perspective on the implementation of 2 new PrEP care modalities. If these modalities are found to be noninferior, they can be easily implemented in routine care using the workflows developed in this study and applied to the 4 participating PHSs. Furthermore, combining monitoring every 6 months and online-mediated PrEP care in this trial offers a unique opportunity to study real-life implementation of these PrEP modalities.

In conclusion, the results of the EZI-PrEP trial will provide evidence on the noninferiority of online-mediated PrEP care compared to in-clinic care and the noninferiority of monitoring every 6 months compared to monitoring every 3 months in terms of PrEP adherence. It will also provide insights into screening every 6 months for HIV infection, STIs, and HCV infection among MSM who use PrEP, and thereby will contribute to the literature on the optimal STI screening frequency among PrEP users. Moreover, the study will investigate to what extent these PrEP care modalities are appealing to PrEP users in general and if particular PrEP users would benefit more from these modalities than others. Finally, the study will provide insights into the sociodemographic and psychosocial factors that influence PrEP adherence. The EZI-PrEP study aims to inform policymakers and sexual health centers in deciding which strategies would be appropriate for PrEP care. The findings will contribute to accessible, low-cost, scalable, and sustainable PrEP care.

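### The noninferiority conclusion is worded as PrEP adherence, but the primary test compares the rate of unprotected acts, of which adherence is only one component

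*Protocol article*

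**What the plan says.** The operative sections of the protocol article define the outcome as HIV-risk behaviour.

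- Study Objectives: the primary outcome is "a condomless anal sex act with a casual partner during which PrEP was not used or insufficiently used".
- Abstract, Methods: the outcome serves "as a proxy for HIV infection risk".
- Data Analysis, Primary Outcome: the rate comes from "dividing the sum of all unprotected acts by the sum of person-years of observation". The text adds: "The analyses will be based on crude unadjusted incidence rate ratios". Noninferiority is concluded if the upper two-sided 97.5% limit is below 1.8.

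The concluding sections describe the same result as adherence.

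- Abstract, Conclusions: whether online and 6-monthly care "is noninferior to standard PrEP care in terms of PrEP adherence".
- Discussion, first paragraph: evidence "in terms of PrEP adherence as a proxy for HIV risk".
- Discussion, on screening frequency: "If noninferiority in terms of PrEP adherence is concluded and STI incidence rates are similar", the case for 6-monthly monitoring as standard of care becomes stronger.
- Discussion, closing paragraph: the "noninferiority of monitoring every 6 months compared to monitoring every 3 months in terms of PrEP adherence".

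**The concern.** An unprotected act needs three things together: casual anal sex, no condom, and insufficient PrEP. Adherence bears only on the third, so a ratio of unprotected acts per person-year is not a ratio of adherence.

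Randomisation balances sexual behaviour at baseline but does not hold it fixed afterwards. The trial is open-label and the modalities change the amount of contact. Under Study Setting, visit counselling covers PrEP intake and other prevention strategies. Under Online PrEP Care, the counselling video consultation becomes optional after 6 months, apart from mandatory ones at 18 and 24 months for study procedures. Condom use and casual sex could therefore respond to allocation as well as pill-taking.

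The wording matters because the Discussion makes noninferior adherence one of two conditions for a stronger case to change the standard of care, and addresses policymakers. A claim that the test does not establish would carry into that decision.

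**Working it through.** **The plan's own figures.** The target of 442 reproduces as 368 × 1.2 = 441.6. The 368 does not reproduce from the stated inputs: common two-group Poisson formulas give totals of 268 to 306. Because 368 is larger, power at 184 per side is about 95% to 97%. This is a separate matter and does not affect the present point.

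**Inputs** (Primary Outcome; Power and Sample Size Calculation; Randomization): rate 0.36 per person-year in both groups; 1.5 years; 368 participants, so 184 per side of each factor; margin 1.8; one-sided alpha 0.0125, so z = 2.2414.

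**Identity.** For each group:

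unprotected acts per person-year = (condomless casual acts per person-year) × (share not covered).

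Hence IRR = (ratio of act rates) × (ratio of uncovered shares). This holds by definition.

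**Largest observed ratio that passes.** Control events: 184 × 1.5 × 0.36 = 99.4. With experimental events equal to 99.4 × IRR:

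- SE(log IRR) = √(1/99.4 + 1/(99.4 × IRR)).
- Upper limit = IRR × exp(2.2414 × SE).
- At IRR = 1.337: SE = √(0.01006 + 0.00753) = 0.1326; upper limit = 1.337 × exp(0.2973) = 1.80.

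So an observed ratio up to about 1.34 passes (about 1.37 with 221 per side).

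**Illustrations.** The component ratios are assumptions. The chance of success is Φ[(ln 1.8 − ln IRR)/SE − 2.2414].

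| Ratio of condomless act rates | Ratio of uncovered shares | IRR | Upper limit if observed | Chance of declaring noninferiority |
|---|---|---|---|---|
| 1.0 | 1.0 | 1.00 | 1.37 | 97% |
| 0.5 | 2.0 | 1.00 | 1.37 | 97% |
| 0.7 | 1.8 | 1.26 | 1.70 | 66% |
| 1.3 | 1.0 | 1.30 | 1.75 | 58% |
| 2.0 | 0.8 | 1.60 | 2.13 | 9% |

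- With 30% fewer condomless acts, the uncovered share can be 1.337/0.7 = 1.91 times as high and an observed result still passes.
- With 30% more acts and identical coverage: SE = √(1/99.4 + 1/129.2) = 0.1334; (0.5878 − 0.2624)/0.1334 − 2.2414 = 0.20; Φ = 0.58.
- The first two rows cannot be told apart by the primary test, although in the second the uncovered share has doubled.

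**What else is compared between arms.** Under Secondary Outcomes, the one direct adherence comparison named is intracellular drug concentration at month 12, by rank-sum test, in daily users only and with no margin. Event-driven users supply intake data by diary and questionnaire, and the Study Objectives plan association analyses involving adherence. No between-arm adherence comparison is named for them.

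**The case against.** The strongest reply is that nothing operative is wrong. The objective, outcome definition, hypothesis and decision rule never claim adherence. The decision rule says only that the intervention arms are noninferior to the comparators, and one of the four adherence statements adds that adherence stands in for HIV risk. This is right as far as it goes: the endpoint is a sound measure of HIV-risk exposure. The fault lies in the stated conclusion, but that is the headline claim, made four times and tied to a policy step, so it is more than loose phrasing.

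Several stronger readings are tempting and are not supported:

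- **That event-driven users have no adherence outcome at all.** They have diary and questionnaire intake data and planned association analyses. Only the drug assay is restricted to daily users, for a stated financial reason.
- **That omitting a split of the rate into its components is itself an error.** The article condenses a fuller protocol, and an analysis plan may hold such an analysis.
- **That the shifts in sexual behaviour are to be expected.** No passage gives their size. A misleading pass needs less contact to reduce condomless sex while coverage worsens, and nothing in the document supports that combination. In the opposite case, more condomless sex at unchanged coverage is a real rise in HIV-risk acts, and failing is then correct for the endpoint; only an adherence label would be wrong.
- **That an observed ratio of 1.30 fails.** Its upper limit is about 1.75, so it passes.

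**Conclusion.** The concern holds as a mismatch between the test and the conclusion drawn from it. The primary comparison can support a statement about the rate of unprotected acts. It cannot by itself support one about adherence, because the crude ratio is a product in which adherence enters through one factor only. Even that factor is not purely adherence, since the uncovered share includes deliberate non-use as well as missed pills.

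The identity needs no assumption. The figures of 1.34, 1.9 times and 58% rest on the plan's rate, follow-up, margin and alpha, on 184 per side, on Poisson variance and on a normal approximation on the log scale. The last two also rest on an assumed 30% shift in condomless acts. They show what the test would allow, not what is likely to happen.

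**What to change.** Keep the primary outcome, margin and test. In the abstract's Conclusions and at the three places in the Discussion, state the result as noninferiority in the rate of unprotected acts (HIV-risk behaviour).

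Alongside it, report two descriptive quantities from the diary, by modality and by monitoring frequency, with confidence intervals that allow for clustering within participants:

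1. the rate of condomless casual acts per person-year;
2. the share of those acts covered by PrEP.

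The diary already records pill intake, casual anal sex and condom use separately for every participant, whichever regimen is used. The covered share is defined only where a condomless act occurred after randomisation, so it is not a clean randomised comparison. It should be labelled supportive and should not act as a formal gate for any claim.

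The cost is one extra analysis of existing data and a narrower headline claim. No new data collection or change in sample size follows.

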**Trial Registration:**

ClinicalTrials.gov NCT05093036; https://tinyurl.com/28b8ndvj

**International Registered Report Identifier (IRRID):**

DERR1-10.2196/51023

## Introduction

Oral tenofovir (TFV) disoproxil combined with emtricitabine (FTC) is highly efficacious as pre-exposure prophylaxis (PrEP) for the prevention of HIV infection [1,2]. PrEP can be taken daily [3-5] or in an event-driven schedule by cisgender men or transgender and gender diverse people (TGDP) assigned male at birth, who are not taking exogenous estradiol-based hormones [6-8]. Globally, the standard of care generally entails in-clinic PrEP initiation and in-clinic monitoring visits every 3 months, including PrEP prescription and dispensing, counseling on PrEP adherence and other HIV prevention strategies, and HIV testing, and may include kidney function testing [8,9]. PrEP programs are recommended to integrate PrEP monitoring visits with testing for bacterial sexually transmitted infections (STIs) and for hepatitis B virus and hepatitis C virus (HCV) infections [8-12]. If combined with the recommended HIV testing frequency, such testing is commonly performed every 3 months, although in practice, the frequency of testing could depend on sexual behavior [8-12].

In-clinic PrEP care faces several challenges that stem from the recommended frequency of monitoring visits (every 3 months). Clients might have to take time off from work, school, or family obligations, and may incur travel costs for attending in-clinic visits [13-17]. Persons interested in PrEP may also feel burdened with perceived stigma [18,19], cultural or social insensitivity [16,20,21], and lack of privacy [14,15] at the clinic. Providers might have capacity problems at facilities owing to shortages of health care staff or budget constraints, and might be forced to limit the number of clients or prioritize certain clients [22-24]. These client and provider barriers may contribute to individuals not initiating PrEP or discontinuing PrEP, which in turn increases the risk of avoidable HIV infections [23,25].

Limiting the number of in-clinic visits by offering online-mediated PrEP care may address some of these barriers [8,26,27]. Different models of digital PrEP services had been implemented across income settings prior to the COVID-19 pandemic, and implementation accelerated since the start of the pandemic [8,26-29]. Online PrEP care generally includes a combination of the following components: telephone or video consultation to collect data regarding medical history, sexual behavior, and PrEP intake, which are needed for PrEP prescription and counseling [8,26-29]; specimen collection for HIV and STI testing at a local laboratory [30], at home using a self-sampling kit [31,32], or a combination of both [30,33]; and delivery of PrEP tablets at locations preferred by users (eg, at home, other addresses, or health facilities) [30,33]. Since online PrEP care involves less intensive contact between PrEP users and health care providers and thus less guidance on PrEP use, it could theoretically have an adverse effect on PrEP adherence. Studies so far have shown high acceptability of online PrEP services among PrEP users. However, these studies were small in scale and were predominantly descriptive in nature and thus did not provide rigorous evidence on PrEP adherence in comparison to the standard of care [29,34], with the exception of an ongoing randomized controlled trial in the United States [31]. In their study, the authors aimed to compare online PrEP care with the standard of care with respect to protective levels of tenofovir diphosphate (TFV-DP) in dried blood spots (DBSs), and the results of this study are still pending [31]. Other trials related to online PrEP care in the European context do not yet exist.

Limiting the number of in-clinic visits through a reduction in the frequency of PrEP monitoring may pose challenges for the timely screening of HIV and other STIs. Regular HIV testing during PrEP use is essential to identify breakthrough HIV infections in suboptimally adherent PrEP users and, rarely, in highly adherent PrEP users [35,36]. It allows for commencing HIV treatment as soon as possible and avoiding onward transmission and the development or transmission of drug-resistant strains. While the current guidelines recommend HIV testing every 3 to 6 months [8-12], few studies have formally investigated the impact of HIV screening frequency on PrEP adherence [8]. A lower frequency of contact moments and HIV testing may negatively affect PrEP intake. One randomized noninferiority trial in Kenya found similar PrEP adherence in adults with dispensing of PrEP every 6 months at the clinic combined with home-sampled HIV testing at 3 months after dispensing and in adults with dispensing of PrEP and HIV testing every 3 months at the clinic as the standard of care [37]. More evidence from other regions and from different groups of PrEP users is needed to further evaluate the implications of reduced frequency of monitoring. Particularly in high income settings with low HIV prevalence and high community-level PrEP uptake and PrEP adherence, HIV testing every 6 months might be sufficient. PrEP monitoring visits for men who have sex with men (MSM) in these settings are commonly combined with STI testing, but the optimal frequency of STI screening among MSM who use PrEP is unknown [2,22,38]. On the one hand, reducing the frequency of PrEP monitoring might lead to delayed diagnosis and treatment of asymptomatic STIs and onward transmission. On the other hand, it might avoid antibiotic use related to asymptomatic chlamydia and gonorrhea [39-41], and a lower STI screening frequency might be sufficient for MSM with lower levels of sexual activity.

The *E-Health for Zero Infections - facilitating access to and use of Pre-Exposure Prophylaxis in the Netherlands* (EZI-PrEP) study has been designed to assess whether online-mediated PrEP care and a reduced frequency of monitoring are noninferior compared to standard practice. The secondary research aims include assessing the effect of reduced monitoring frequency on HIV and STI testing behaviors and assessing whether the frequency of testing matches the level of behaviors associated with acquiring these infections. In the EZI-PrEP study, we will develop, implement, and evaluate an online-mediated PrEP care service and a less frequent monitoring schedule (every 6 months) among MSM and TGDP in 4 regions in the Netherlands. This paper describes the design and methods of the EZI-PrEP study.

